# Study protocol for a randomized controlled trial testing the efficacy of Emotion Detectives In-Out: a blended version of the unified protocol for transdiagnostic treatment of emotional disorders in Portuguese children

**DOI:** 10.1186/s40359-024-01532-z

**Published:** 2024-02-07

**Keywords:** Unified protocol for children, Emotion Detectives In-Out, Coping cat, Randomized controlled trial, Children, Anxiety disorders

## Abstract

**Background:**

Childhood emotional disorders (EDs; i.e., anxiety and depressive disorders) are currently a public health concern. Their high prevalence, long-term effects, and profound influence on the lives of children and families highlight the need to identify and treat these disorders as early and effectively as possible. This clinical trial will examine the efficacy of a blended version (i.e., combining face-to-face and online sessions into one treatment protocol) of the Unified Protocol for Children (the “Emotion Detectives In–Out” program). This program is a manualized cognitive-behavioral therapy for the transdiagnostic treatment of EDs in children aged 7 to 12 years that aims to reduce the intensity and frequency of strong and aversive emotional experiences by helping children learn how to confront those emotions and respond to them in more adaptive ways.

**Methods:**

This study is designed as a multicenter equivalence randomized controlled parallel-group two-arm trial comparing the Emotion Detectives In–Out program with an evidenced-based group intervention for children with anxiety disorders (the Coping Cat program). Participants will be children aged between 7 and 12 years with an anxiety disorder or with clinically significant anxiety symptoms as well as one of their parents or a legal representative. A minimum sample size of 138 children (69 per group) is needed to test whether the efficacy of the proposed intervention is equivalent to that of the well-established Coping Cat intervention.

**Discussion:**

We expect Emotion Detectives In–Out to be a feasible and efficacious alternative intervention for treating children's EDs by allowing for a greater increase in children's access to care. A blended format is expected to overcome common barriers to treatment (e.g., parents´ lack of time to attend regular sessions) and make the intervention more accessible to families.

**Trial registration:**

The clinical trial is registered at ClinicalTrials.gov (Identifier: NCT05747131, date assigned February 28, 2023).

**Supplementary Information:**

The online version contains supplementary material available at 10.1186/s40359-024-01532-z.

Childhood emotional disorders (EDs), such as anxiety and depressive disorders, are currently considered an important public health concern [1]. The prevalence of these problems has been growing in recent years [2–4], particularly during and after the COVID-19 pandemic. A recent meta-analysis of the global prevalence of children’s and adolescents’ clinical levels of depression and anxiety symptoms during the COVID-19 pandemic estimated a pooled prevalence of 25.2% for depression symptoms and 20.5% for anxiety symptoms [5], which is more than double the estimated prevalence of both types of symptomatology in the prepandemic period. EDs in childhood significantly impact children´s functioning at multiple levels (e.g., family, academic, social) [6] and have long-term consequences. For instance, it is estimated that half of all mental health problems in adulthood have their onset before the age of 14 years [4, 6]. EDs also represent a societal burden; for example, families of children with anxiety disorders have 20 times higher costs than families from the general population [7]. It is therefore critical to recognize and treat EDs as early as possible.

Nevertheless, there is a considerable gap between children’s needs and their actual access to mental health care. The majority of children remain untreated due to a lack of access to psychological treatment, particularly evidence-based treatment (EBT) [8]. One of the key reasons for the absence of adequate mental health treatment is the inability of pediatric mental health public services to provide these children with a prompt and effective response. On the one hand, there is a lack of trained clinicians in many pediatric mental health public services. On the other hand, face-to-face therapy continues to be parents’ preferred intervention modality [9–11]. In addition, it is frequently the only delivery format offered in pediatric services, which contributes to lengthy wait lists and extended gaps between therapy sessions.

Many barriers may prevent parents from seeking face-to-face therapy for their children, such as a lack of time to attend regular sessions, costs associated with time off work and travel, and a lack of motivation to commit to lengthy face-to-face treatment [12]. Therefore, it is urgent to improve the accessibility of EBTs for childhood EDs in public mental health systems. Internet-based psychological interventions can be an effective solution for overcoming these difficulties [13, 14].

In this study, we will test the efficacy of a blended version (i.e., a combination of face-to-face and online therapy in one integrated treatment protocol [15]) of the Unified Protocol (UP) for the transdiagnostic treatment of emotional disorders in children (UP-C; [16]). The UP-C is a cognitive‒behavioral therapy (CBT) that adopts a transdiagnostic approach to treat multiple EDs simultaneously by addressing the shared mechanisms underlying these disorders (e.g., neuroticism) and combining EBT strategies (e.g., exposure, mindfulness, cognitive flexibility). It is an adaptation of the adult UP [17] for children aged 7 to 13 and delivers the key components of the UP in an interactive and child-friendly group format with considerable parent involvement. A pilot randomized controlled trial (RCT) comparing the UP-C with an anxiety-specific EBT (Cool Kids; [18]) found that both treatments were effective in treating anxiety, but the UP-C resulted in greater improvements in depression and emotion regulation [19].

In addition to its promising efficacy, the UP-C has important advantages over other EBTs, making it scalable and easily implementable in child mental health services. For instance, the UP-C is a group therapy that enables the simultaneous treatment of 7–8 children with different EDs, thereby reducing the costs associated with individual treatment for families and institutions and minimizing the therapist’s burden [20]. In addition, focusing on the core mechanisms underlying different EDs may have favorable long-term outcomes [21]. Another critical advantage is that unlike most psychological interventions for children, it includes the same number of sessions for parents that focus on parental behaviors that are known to be critical risk and maintenance factors of EDs in childhood (e.g., parental criticism, overprotection, modeling of intense emotions and inconsistency) [22]. Furthermore, there is evidence that the efficacy of CBT improves significantly when caregivers are more involved in their children’s treatment [23].

While the UP-C is a promising approach to treating childhood EDs, the demand for face-to-face therapy exceeds the capacity of child mental health services [24], and many barriers prevent parents from seeking face-to-face therapy for their children. Internet-based interventions can overcome these barriers and provide an easily accessible option that may significantly increase access to care [25]. Importantly, internet-based interventions may be particularly appealing to children, who are typically early adopters and regular users of new technologies [26]. In addition, there is evidence that internet-based interventions (e.g., BRAVE-online; [27]) are effective in reducing children’s EDs [14, 28–30] and are acceptable to children, families and clinicians [11, 31–34]. However, certain drawbacks to interventions conducted exclusively online have been recognized, including the absence of direct clinician interaction, limited effectiveness in addressing severe mental health issues, and elevated rates of participant dropout [35, 36]. A blended format can overcome these limitations and make psychological therapy more accessible to families [15].

Therefore, a blended version of the UP-C, the Emotion Detectives In–Out, was developed to improve the delivery of the UP-C by retaining the positive aspects of face-to-face and online therapy while mitigating their disadvantages [37, 38]. This new version is expected to reduce therapy costs for families and institutions, improve compliance, increase motivation, enhance the uptake of treatment principles, and facilitate the generalization of the application of core treatment components [39].

## Objectives

The main goal of this clinical trial is to test the efficacy of the Emotion Detectives In–Out intervention in reducing children’s anxiety symptoms and changing secondary outcomes in comparison to an active control group, the Coping Cat intervention, an EBT for children with anxiety [40]. A multicenter equivalence RCT will be used to answer the critical question of whether the Emotion Detectives In–Out intervention has at least as much efficacy as the active control group in reducing anxious symptomatology and changing secondary outcomes [41]. The Emotion Detectives In–Out intervention is expected to be as effective as the Coping Cat while presenting important advantages, including greater availability, reduced cost for families and institutions, a lower therapist burden, and greater parental involvement. In this clinical trial, we also aim to identify key factors that may predict adherence to the Emotion Detectives In–Out and that may predict treatment outcomes.

## Methods

### Trial design

This study is designed as an equivalence randomized controlled parallel-group two-arm trial (allocation ratio 1:1) to compare a new blended group intervention (Emotional Detectives In–Out) with a face-to-face group intervention (Coping Cat) for children with anxiety disorders. The Coping Cat intervention was chosen as the active control group because it is an evidence-based cognitive-behavioral intervention for children with anxiety disorders [40, 42] that can be used to test the equivalence of the Emotion Detectives In–Out intervention in reducing anxiety symptomatology. An equivalence trial aims to demonstrate that a novel or non-established treatment is as effective as a well-established treatment within a prespecified margin of equivalence. In the current trial, the margin of equivalence was defined as the difference between the intervention groups that would be considered the minimum clinically relevant difference.

The clinical trial is registered at ClinicalTrials.gov (identifier: NCT05747131, date assigned February 28, 2023). Authorization for sample recruitment was obtained from the Ethics Committee of the Faculty of Psychology and Education Sciences of the University of Coimbra and from the Ethics Committee of the Faculty of Psychology of the University of Lisbon. The clinical trial will follow the ethical recommendations of the American Psychological Association (APA, 2010) and the World Medical Association’s Declaration of Helsinki (World Medical Association, 2013).

The SPIRIT (Standard Protocol Items: Recommendations for Intervention Trials) checklist of information [43] and the CONSORT recommendations for noninferiority and equivalence trials [41] will be used as guidance to report the study protocol of this clinical trial.

### Participants

The participants will be children aged 7 to 12 years with an anxiety disorder or subclinical anxiety symptoms as well as one of their parents or a legal representative. The following eligibility criteria will be considered:The child is aged 7 to 12 years;The child has a primary diagnosis of an anxiety disorder or clinically significant anxiety symptoms;Both the child and the parent/legal representative are able to speak, read and understand Portuguese;Both the child and the parent/legal representative have internet access;The child does not have a diagnosis of a psychotic disorder, bipolar disorder, intellectual disability or autism spectrum disorder;The child does not have severe current suicidal ideation;The child is on a stable dose of psychotropic medication for at least 1 month prior to the baseline assessment;The child is not currently receiving other types of psychotherapy.

### Study procedures

The SPIRIT schedule of enrollment, interventions, and assessments is presented in Fig. 1.

**Fig. 1 Fig1:**
[figure not shown]
Schedule of enrollment, interventions, and assessments

#### Participant recruitment

Participants will be recruited in public hospitals and schools from different locations in Central Portugal and the Lisbon Metropolitan Area. At the child mental health services of the collaborating hospitals, children who are having a first visit with a mental health specialist will be referred to the clinical trial based on a preliminary evaluation of the child’s symptomatology and the clinical judgment that the child would benefit from a group intervention. Parents and children who agree to participate in the trial will be contacted by the research team to schedule the eligibility interview. At schools, the teachers and psychologists who are collaborating in the study will refer children previously identified as potentially having an ED. The research team will then contact the parents to confirm the main eligibility criteria and schedule the eligibility interview. Teachers will also be asked to disseminate the project via email to all parents, who will be able to enroll in the project through a link provided in the email. Finally, parents will have the opportunity to contact the research team directly via email and express their desire to enroll their child in the trial after obtaining information about the study through the project’s social media platforms or from flyers distributed at mental health services at hospitals and schools.

All parents will be informed that they are being invited to participate in a clinical trial that will assess the efficacy of two psychological interventions for children with anxiety disorders: the Emotion Detectives In–Out and the Coping Cat. They will not be informed about which intervention is the experimental or the control condition.

#### Participant selection

The eligibility criteria for the study will be assessed in an initial interview with parents and children. First, a researcher will briefly explain the goal and procedures of the study and the initial interview and will ask both the parents and the child for consent to administer the Anxiety Disorders Interview Schedule for Children (ADIS-IV-C) [44]. The ADIS-IV-C is a semistructured interview for assessing the presence of anxiety difficulties and diagnosis (e.g., separation anxiety, social phobia, specific phobia, panic disorder, agoraphobia), obsessive–compulsive disorder, posttraumatic stress disorder, depressive disorder, and externalizing disorders (e.g., attention deficit and hyperactivity disorder) in youth aged 6 to 17 years according to the diagnostic criteria of the Diagnostic and Statistical Manual of Mental Disorders (DSM-IV; APA, 1994). Parents and children will be interviewed together by a clinical psychologist, according to the procedure described by Khanna and Kendall [45]. In the case of differences between the parent's and child's responses to an item, we will adhere to the guidelines provided by Grills and Ollendick [46]. This involves consolidating both reports and employing an “OR” rule to determine the presence of a symptom or diagnosis. Therefore, information gathered from the parent and the child will be merged and considered in making the final diagnostic decisions. Each disorder will receive a clinician severity rating (CSR) ranging from 0 to 8. A CSR of 4 or greater indicates the presence of a clinical diagnosis. The principal diagnosis will be the disorder(s) with the highest CSR. If a child exhibits some symptoms of a disorder but does not meet all the criteria and these symptoms affect daily functioning, the condition will be categorized as subclinical.

The absence of a diagnosis of a psychotic disorder, bipolar disorder, intellectual disability, autism spectrum disorder, and current suicidal ideation as well whether the participants have internet access to complete online sessions and proficiency in Portuguese will also be assessed during the initial interview. The child´s medication will be confirmed with the child´s pediatrician/psychiatrist or with the parents. This initial interview is expected to last approximately 90 min.

Parents will be informed at the end of the interview if their child meets the eligibility criteria for enrollment in the clinical trial. Parents of eligible children will be provided with detailed oral and written information about the next phase of the study and will be asked to provide written informed consent, and children will be asked to provide their assent. The researchers will orally explain the main characteristics of the study and will answer all of the participants’ questions, both during the eligibility interview and throughout the implementation of the study. Parents and children will receive adequate information about the clinical trial in a way that they can understand to enable them to make an informed decision. Specifically, among other aspects that are common to the majority of clinical trials (e.g., voluntary participation in the study, guarantee of anonymity and confidentiality), the researchers will inform the parents/legal representatives about a) the experimental design of the study and its main characteristics; b) alternative treatment options if the parents and/or the child decide not to participate in the study or choose to withdraw; and c) the absence of monetary costs associated with participation. After providing informed consent/assent, the parents and children will fill out the baseline (T0) assessment measures.

If a child refuses to participate, even if the child’s parents have signed the informed consent form, the child will not be included in the study and will be referred to a mental health specialist within the health or school institution where the child was recruited. Participants who do not meet the inclusion criteria will be duly informed about the reasons for their exclusion from participation. If these reasons are due to the presence of a serious psychiatric disorder or other difficulty requiring mental health support (e.g., psychotic or behavioral problems as the main diagnosis), the parents will immediately receive recommendations about the best type of medical/psychological support, and the psychologist or psychiatrist of the health service or school will be notified.

#### Sample size

A minimum sample size of 138 children (69 per group) is needed to test the equivalence between two interventions that do not differ by more than the minimum expected effect size of *d* = 0.50, which is slightly larger than the recommended minimum practical effect size indicated by Ferguson [47]. This calculation is based on the two one-sided tests (TOST) procedure for determining equivalence as outlined by Lakens [48] and using the authors´ TOSTER package for R, assuming equal group allocation, alpha = 0.05, 80% power, and four measurements. This sample size is also sufficient to detect within-subject changes in anxiety scores of the same magnitude (*d* = 0.50) over four measurements (WebPower; [49]). With this sample and allowing for a substantial violation of sphericity, the achieved power is 97%. Finally, an *N* = 138 with four measurements is sufficient for growth mixture modeling [50]. With an attrition rate of 15% [19, 51], we will have to recruit approximately 165 parents at T0 to achieve the final intended sample size.

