#### Randomization

##### Sequence generation

After the children and parents fill out the baseline (T0) assessment measures, they will be randomly assigned at each recruitment location by a researcher not collaborating in the study and through an automated, web-based randomization program to one of two conditions: the experimental condition (Emotion Detectives In–Out) and the active control condition (Coping Cat). A permuted block randomization procedure will be employed in each location to obtain groups with an equivalent number of participants. The block size will depend on the number of eligible children in each location, but it is expected to be between 10 and 12 so that 5 to 6 participants can be assigned to each condition.

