### Interventions

#### Emotion Detectives In-Out

The Emotion Detectives In–Out program is a blended cognitive-behavioral intervention for children aged 7 to 12 years with emotional disorders and their parents. It is a transdiagnostic and emotion-focused manualized treatment designed to help children reduce the intensity and frequency of strong and aversive emotional experiences and to help parents reduce parental emotional behaviors. The standard version [16] includes a set of CBT techniques (e.g., problem-solving, mindfulness, cognitive flexibility, exposure) that are presented to the children and parents through the analogy of an “emotion detective” and are organized into five primary sections around the acronym CLUES (C: “Consider How I Feel”; L: “Look at My Thoughts”; U: “Use Detective Thinking”; E: “Experience My Fears and Feelings”; and S: “Stay Healthy and Happy”). In the blended version, the mindfulness skill will be implemented from session 4 onward until the program's conclusion, with each session commencing with a short mindfulness exercise. The concept of self-compassion (nonjudgmental awareness) will be introduced in session 4. The blended UP-C maintains the same 15 weekly sessions for children as the standard UP-C, but 10 of these are face-to-face group sessions, three are online self-guided sessions, and two are online therapist-guided sessions through videoconference. Face-to-face sessions have an expected duration of 90 min. They will include approximately 5–6 children and will be implemented by one clinical psychologist. The online sessions are entirely self-guided and will last approximately 45 min (see Table 1).

**Table 1 Tab1:** Session-by-session description of the emotion detectives in–out psychological intervention (Children)

Children		
Session	**Theme**	**Format Delivery**
1	Introduction to the Emotion Detectives In–Out program	F2F
2	Getting to know my emotions (psychoeducation about emotions)	F2F
3	My body sensations	F2F
4	Using science experiments to change our emotions and behaviors (acting opposite) and introduction to mindfulness and self-compassion	F2F
5	Identify my thoughts (flexible thinking and thinking traps)	OSG
6	Detective thinking	F2F
7	Problem-solving	OSG
8	Introduction to emotion exposure	F2F
9	Review emotion detectives’ skills and safety behaviors	OSG
10	Exposure (group exposure and individual exposures)	F2F

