#### Coping cat

Coping Cat is a cognitive behavioral therapy for children aged 7 to 13 years with anxiety disorders. In the first segment of the intervention, the children acquire several strategies that help them manage anxiety (i.e., recognizing anxiety through the identification of body cues; managing physiological activation through relaxation and diaphragmatic breathing; identifying and modifying negative automatic thoughts through cognitive restructuring; problem-solving; self-reward). The children integrate the strategies learned into a fear plan using the acronym FEAR (F = Feeling Frightened; E = Expecting Bad Things to Happen; A = Attitudes and Actions that Can Help; and R = Results and Rewards). Once the children develop these skills, they are better able to face anxiety-producing situations. Therefore, the intervention's second segment focuses on gradual exposure to anxiety-producing situations. In- and out-session group and individual exposure tasks are conducted with the children. The group version of the Coping Cat program consists of 16 weekly group sessions with 5 to 7 children per group and two individual sessions with the parents (see Table 3). The face-to-face sessions have an expected duration of 90 min and will be implemented by one clinical psychologist.

**Table 3 Tab3:** Session-by-session description of the group coping cat psychological intervention

Session	Theme	Participant
**1**	Introduction to the Coping Cat program	Child
**2**	Psychoeducation about emotions	Child
**3**	Recognizing somatic responses to anxiety	Child
**4**	Managing the somatic component of anxiety	Child
**5**	Recognizing and modifying negative cognitions	Child
**Parents’ sessions (during weeks 4 & 5)** Encouraging parental cooperation with the treatment program and gathering additional information about each child		Parents
**6**	Recognizing and modifying negative cognitions and problem-solving	Child
**7**	Developing realistic self-evaluations and using self-reward	Child
**8**	Fear plan review	Child
**Parents’ session (during weeks 8 & 9)** Updating information about each child, reviewing and summarizing the skills presented during the half part of the program, encouraging parental cooperation with the exposure segment of the treatment, and working with parents to design in vivo experiences tailored to each child		Parents
**9–11**	Exposure	Child
**12–15**	Exposure	Child
**16**	Conclusion	Child

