### Statistical methods

#### Efficacy evaluation

The efficacy of the Emotion Detectives In–Out in comparison with the Coping Cat will be assessed by analyzing the changes in the primary and secondary outcomes. As an equivalence clinical trial, the aim is to test whether the Emotion Detectives In–Out (experimental condition) is as effective as the Coping Cat (control group). The planned analysis for each outcome is a repeated-measures linear mixed model adjusted for covariates. The primary equivalence testing will be the between-group difference TOST at postintervention and at 3 months using the Welch correction for heterogeneous variance if needed. We will also investigate the linear and nonlinear (quadratic) effects for time and condition and simple effects for parameter estimates within each condition. For categorical variables (e.g., treatment response as assessed by CGI-I), treatment conditions will be compared using Pearson’s chi-square test.

To examine for heterogeneous intervention response, we will calculate Reliable Change Indices (RCI) for all participants at postintervention and at the 3-month follow-up. The RCI will be calculated for all outcomes and correlated with demographics to examine for subgroup efficacy predictors. The cutoff for clinically significant change is generally accepted as ± 1.96 [81]. Likewise, we aim to test the longitudinal trajectory of anxious symptoms over time using Growth Mixture Modeling (GMM). Furthermore, assuming that heterogeneous trajectories of anxious symptoms are observed, we aim to test the suitability of the collected demographic variables as predictors of group membership.

For the primary equivalence, efficacy, RCI, and chi-square analyses, we will use Jamovi software and the GAMLj and TOSTER packages as needed [82]. For GMM analyses, we will use R software with the package *lccm* [83] to perform growth mixture modeling, and evaluate various model specifications of *k* classes two through six, and using both fixed and random effects. We will select the optimal number of clusters was based on four criteria: parsimony, entropy approaching 1, lowest BIC/SABIC, and minimum class size > 10% of the sample [84, 85].

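### The sample size and the primary TOST make no allowance for clustering by therapy group, although both arms are treated in therapist-led groups of about 5 to 7 children

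*Protocol article*

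**What the plan says.** The Sample size section of the protocol article states: "A minimum sample size of 138 children (69 per group) is needed to test the equivalence between two interventions". The margin is that the interventions "do not differ by more than the minimum expected effect size of *d* = 0.50". On method it says "This calculation is based on the two one-sided tests (TOST) procedure for determining equivalence", and the remaining inputs are "assuming equal group allocation, alpha = 0.05, 80% power, and four measurements". No ICC, design effect or number of therapy groups is given.

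Treatment is delivered in groups in both arms. For Emotion Detectives In-Out, 10 of the 15 child sessions are face-to-face group sessions. Groups are expected to hold about 5 or 6 "children and will be implemented by one clinical psychologist". Coping Cat has "16 weekly group sessions with 5 to 7 children per group", also led by one psychologist. Under Sequence generation, randomisation is in permuted blocks within location, with an expected block size of 10 to 12 "so that 5 to 6 participants can be assigned to each condition".

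Efficacy evaluation says: "The primary equivalence testing will be the between-group difference TOST at postintervention and at 3 months using the Welch correction", the correction applying only if needed. The same paragraph plans a covariate-adjusted repeated-measures mixed model for each outcome. Neither that section, nor Covariates, nor the missing-data section names a term for therapy group, therapist or location.

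**The concern.** Children in one therapy group share a psychologist, peers, sessions and group exposure work, so their outcomes may be positively correlated. If they are, the arm difference varies more than an independent-children calculation assumes. This has two consequences.

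- A correct analysis of 138 children has less power than stated.
- A two-sample TOST without a group term uses a standard error that is too small, so its 90% CI is too narrow. In an equivalence trial this error favours the hoped-for conclusion: a programme whose true difference lies at the margin is declared equivalent more often than 5% of the time.

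**Working it through.** **Inputs from the article.** Margin 0.50 SD; alpha 0.05 for each one-sided test; power 80%; 69 analysed per arm; about 165 recruited; 5–6 children per condition per block; Coping Cat groups of 5–7.

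**Assumptions, not in the article.** True difference zero; a common ICC in both arms of 0.01, 0.02, 0.05 or 0.10; m = 4.6 to 6 analysed children per group. The lower m allows for attrition: 165/2 = 82.5 per arm, 82.5/5.5 = 15 groups, and 69/15 = 4.6. The upper m is a full half-block with no loss.

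**1. Reproduce the stated figure.** n per arm = 2 × ((1.645 + 1.282)/0.50)² = 68.5, rounded up to 69. Power at 69 is 80.4% by the normal approximation and 79.9% with t quantiles. Independent children are therefore the basis of the figure. The reference to four measurements is not needed to reach it, and repeated measures on one child do not address correlation between children.

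**2. Formulas under clustering.**
- Design effect DE = 1 + (m − 1) × ICC
- SE of the standardised difference = √(2 × DE/69)
- Power of a clustering-aware TOST, normal approximation = 2Φ(0.5/SE − 1.645) − 1
- False-equivalence rate at the margin when groups are ignored ≈ Φ(−1.645/√DE)

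Example, m = 6 and ICC 0.05: DE = 1 + 5 × 0.05 = 1.25; SE = √(2.5/69) = 0.190; 0.5/SE − 1.645 = 0.98; power = 67.4%. False equivalence: Φ(−1.645/1.118) = Φ(−1.471) = 7.1%.

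Power was also computed with t quantiles on group-level df = 2k − 2, where k = 69/m groups per arm (df 28 at m = 4.6, df 21 at m = 6).

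**3. Results.** The first value in each cell is for m = 4.6, the second for m = 6.

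| ICC (assumed) | DE | Power, normal approx. | Power, group-level df | False equivalence if groups ignored |
|---|---|---|---|---|
| 0 | 1.00 | 80.4% | 77.7%, 76.8% | 5.0% |
| 0.01 | 1.04, 1.05 | 78.5%, 77.8% | 75.8%, 74.0% | 5.3%, 5.4% |
| 0.02 | 1.07, 1.10 | 76.7%, 75.2% | 73.8%, 71.2% | 5.6%, 5.8% |
| 0.05 | 1.18, 1.25 | 71.0%, 67.4% | 67.9%, 63.0% | 6.5%, 7.1% |
| 0.10 | 1.36, 1.50 | 61.8%, 54.9% | 58.3%, 50.1% | 7.9%, 8.9% |

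The ICC 0 row shows that group-level df alone cost 2 to 3 points against the t-based 79.9%. That part of the loss is the price of estimating variance from few groups and does not come from correlation.

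**4. Simulation check.** With 12 groups of 5–6 per arm (69 children), a Welch TOST that ignores groups gave false equivalence of 5.5%, 5.8%, 6.9% and 8.8% at ICC 0.01, 0.02, 0.05 and 0.10. An analysis of group means gave power of 74.1%, 71.4%, 63.6% and 51.1%. These agree with the table. The TOST that ignores groups also misses 80% power: 75.0% at ICC 0.05 and 70.9% at 0.10.

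**5. Size needed for 80%, by the normal approximation.** With 5 to 6 per group, about 166–172 analysed children at ICC 0.05 and 192–206 at ICC 0.10, against 138.

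**The case against.** **The ICC is unknown and may be small.** This stands as a limit on size. At 0.01 the error rate barely moves and power falls by only about 2 points under the normal approximation. A reader might infer that the stated 80% and 5% are shown to fail by a known, large amount. The article does not support that. What it shows is that no allowance was made.

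**Some variance cancels.** Randomisation is blocked within location, so variation shared by both arms at a location drops out of the contrast, and an unadjusted test is conservative for that part. Only variance specific to one arm's therapy group or therapist counts. Therapists are trained in both programmes. If the same psychologist leads groups in both arms, which the article does not say, part of the therapist variance cancels too. A third of the experimental arm's child sessions are online, so one ICC for both arms is a simplification.

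**The unseen analysis plan may add a group effect.** Random-effects structure is often left to that document, and the mixed model here lists no random effects at all. So silence does not prove that a therapy-group effect is excluded, and the Welch correction is itself conditional. This weakens the analysis half of the point: a later plan could repair the test. It could not repair the published sample-size statement.

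**Each block need not be one therapy group per arm.** That is also only an inference, because block size is described as expected and dependent on local numbers. The group sizes stated under Interventions are enough for the calculation. Where Coping Cat groups reach 7, the loss is somewhat larger than tabulated.

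**Conclusion.** The point holds as an omission in the plan as published. Both arms are delivered in groups, 69 per arm is exactly the independent-children number, and the test named as primary carries no therapy-group term. Any positive ICC arising within an arm's groups lowers power below the stated 80% and, if groups are ignored, raises false equivalence above 5%.

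The size is conditional on the assumed ICC. It is minor at 0.01, clear for power from about 0.02 (71–77%), and material at 0.05 to 0.10, where power is between 50% and 71% and false equivalence between 6.5% and 8.9%. These ranges assume 69 analysed per arm, 4.6 to 6 per group, equal ICC in both arms and a true difference of zero. Lower power values use group-level df; upper values use the normal approximation.

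A reader might also infer that adjusting for baseline would restore 80% without more children. The article gives no baseline-outcome correlation, and it is not known whether adjustment would reduce variance that arises after groups form. No such claim is made here.

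**What to change.** 1. Record a therapy-group identifier for every child.
2. Define the primary equivalence test as the 90% CI for the arm contrast from the mixed model already planned, with a random intercept for therapy group, small-sample degrees of freedom, and location in the model. Compare that CI with the ±0.50 SD margin, in place of a two-sample TOST without a group term.
3. In Sample size, replace the 80% claim with the power at 138 children over a stated ICC range, for example 0.01 to 0.10, giving the group size and df used. The team can then judge whether that power is acceptable.

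The cost is one recorded variable and revised wording. The stated power becomes less favourable and the primary CI slightly wider. Treatment delivery does not change.
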